#### Healthcare CEO App Chat Room Data Analysis

Chats in the CEO Chat Rooms will first undergo thematic categorization, beginning with a review of the chat content to gain an initial understanding. Relevant patterns will then be identified and labeled through initial coding, and similar codes will be grouped to form broader themes. These themes will be reviewed and refined for relevance and consistency with the data, and each theme will be clearly defined. Finally, the frequency of each identified theme will be calculated.

### Ethical Considerations

The study will follow the Declaration of Helsinki and has received approval from the Ethics Committee of the Chang Gung Foundation Institutional Review Board (submission reference: 202100050B0; March 9, 2021). It will uphold key ethical principles, including informed consent, with participants receiving comprehensive information about the study. For minors, consent will be obtained from a legal guardian simultaneously, and efforts will be made to minimize any undue influence from guardians or family members to guarantee voluntary participation. Participants may withdraw at any time without impacting their medical care. The study prioritizes participant safety through self-reported questionnaires and a mobile app that poses no risks. Justice is maintained by ensuring equal medical care for all participants, with the control group accessing the app after the study. Privacy is protected with data secured in locked storage and coded identifiers used in publications to ensure anonymity. Participants will receive a voucher worth NT $300 (approximately US $9.34) for each completed questionnaire as an appreciation for their time and effort.

### Validity and Reliability

The study design and participant enrollment process were formulated in accordance with the recommendations of the CONSORT (Consolidated Standards of Reporting Trials) statement. We also formulated strategies based on the National Institution of Health Behavior Change Consortium guidelines to monitor the faithfulness and fidelity of the intervention process. The research tools used in this study also exhibit good validity and reliability. In the measurement of the primary outcome variables, this study differs from previous works on diabetes management apps in that “% with HbA_1c_ <7.0%” data will be calculated for the first time for analysis. This allows for greater objectivity and rigor in evaluating the effectiveness of the Healthcare CEO app.

## Results

After a comprehensive review, the National Science and Technology Council, Republic of China (MOST 109-2314-B-182-057-MY2), and Chang Gung University (NMRPD1K1021) provided financial support for this research project. The project was initially scheduled to run from August 1, 2020, to July 31, 2022. However, owing to the widespread impact of the COVID-19 pandemic, the study was abruptly halted after the enrollment of 38 participants. Details of the recruitment and randomization processes can be found in the CONSORT flowchart (Figure 3). We anticipate that the preliminary results will be compiled and submitted for publication by November 2024. The recruitment of participants resumed in August 2023, with findings expected to be finalized by July 2025. At present, each experimental and control group includes 13 participants.

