**Results:**

The study was funded in August 2020. It was originally scheduled from August 2020 to July 2022 but was interrupted by the COVID-19 pandemic after enrolling 38 participants, with preliminary results anticipated for publication by November 2024. Recruitment resumed in August 2023, with findings expected to be finalized by July 2025.

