#### Sample Size

The required sample size was estimated using the G*Power program (Heinrich-Heine-Universität Düsseldorf) for repeated measures with 2 groups, 9 measured variables, power of 0.80, α set at .05, an estimated Cohen effect size of 0.25, and a correlation coefficient of 0.5. The sample size for each group was calculated as 36. By allowing for a potential 25% dropout rate, as suggested by Goyal et al [31], a final sample size of 96 participants (48 participants in each group) was established.

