### Data Analysis

#### Statistical Analysis

The intention-to-treat principle will be used for the data analysis; that is, all participants will be included in their initially assigned groups for analysis, regardless of whether they withdraw from the study for any reason or are lost to follow-up. Data will be analyzed using IBM SPSS 26.0 for Windows, with differences considered statistically significant at *P*<.05. Demographic and disease status data, including age, gender, BMI, age at diagnosis, disease duration, and HbA_1c_, along with metrics on the app usage to evaluate treatment fidelity, such as the log-ins to the app, frequency of use for each interface, number of e-books read in the CEO Knowledge Base, and number of online consultations in CEO’s Secretary, will be presented through descriptive statistics. This will include frequency distributions, percentages, means, SDs, and maximum and minimum scores. Homogeneity in the essential attributes of the 2 groups will be compared and analyzed using inferential statistics, such as the chi-square test and ANOVA. Owing to the longitudinal nature of this study, repeated data measurements will be taken. Dependencies may exist among the data at different time points, and data loss may also occur. Using generalized estimating equation models, repeated measurements can be simultaneously included in the regression analysis. Through the variance correction process, consistent estimates of the regression parameters and their variance can be provided to correct for dependencies, and participants with missing values can still be included in the analysis [52]. Therefore, a generalized estimating equation will be used for data analysis to compare the differences between the experimental and control groups at both preintervention and postintervention time points, as well as the differences in the scores of the experimental group before and after intervention.

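### Preliminary results are to be submitted while the trial is probably still in follow-up, although the stated design has a single look; if they compare the arms, this is an interim look that the design does not account for

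*Protocol article*

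**What the plan says.** The Results section of the protocol article states: "We anticipate that the preliminary results will be compiled and submitted for publication by November 2024". The Results paragraph of the abstract puts it slightly differently, "with preliminary results anticipated for publication by November 2024", in the same sentence that reports the interruption after 38 participants. The Results section continues: "The recruitment of participants resumed in August 2023, with findings expected to be finalized by July 2025". It adds that each group currently has 13 participants and does not explain how that figure relates to the 38.

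The design sections describe one analysis. Sample Size gives "power of 0.80, α set at .05, an estimated Cohen effect size of 0.25, and a correlation coefficient of 0.5", leading to 36 per group, and 96 in total after a 25% dropout allowance. Statistical Analysis gives one threshold: "with differences considered statistically significant at *P*<.05". Data Collection sets outcome visits at 3, 6 and 9 months (T1 to T3). Randomization and Blinding says that participants and data collectors are blinded; Limitations says that researchers are not.

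**The concern.** The article plans to release results of the trial before the trial ends, but its sample size and significance threshold assume one analysis at the end. Two things could follow if the preliminary paper compares the arms.

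- **Operational bias.** The secondary outcomes are self-report questionnaires. Randomization and Blinding tries to equalise expectations by telling every participant that app use is potentially beneficial. A published by-arm result would say which version performs better, and the versions are easy to tell apart: eleven interfaces against two. Data collectors, and the attending physicians who refer patients, could be influenced as well.
- **Error rate.** If the same participants are tested early at .05 and again at the end at .05, and either result counts as evidence of efficacy, the chance of a false claim exceeds 5%.

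**Working it through.** **1. The plan's own sample size.** Inputs from Sample Size: 2 groups, f = 0.25, correlation ρ = 0.5, m = 9, α = .05, power 0.80. The between-groups repeated-measures F test has noncentrality λ = f²·N·m / (1 + (m − 1)ρ), with 1 and N − 2 degrees of freedom.

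- N = 72: λ = 0.0625 × 72 × 9 / (1 + 8 × 0.5) = 40.5 / 5 = 8.1; power 0.801. This gives 36 per group, as stated.
- Dropout: 36 / (1 − 0.25) = 48 per group, 96 in total, as stated.

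The figure reproduces with the whole .05 spent at one final test.

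**2. Timeline.**

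- For the last T3 visit to fall by July 2025, the last enrolment must be by about the end of October 2024 (July 2025 less 9 months).
- Anyone enrolled after about February 2024 would still be in follow-up in November 2024.
- When the article was written, each group had 13 participants against 48 planned. Follow-up is therefore likely to overlap November 2024; on these dates, overlap with recruitment is not certain.
- Participants outside the first 38 number at most 96 − 38 = 58. Those enrolled soon after August 2023 could have finished T3 by then, so 58 is a ceiling.

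**3. Type I error of two looks.** This is conditional on three things: the arms are tested at .05 at both looks, the early participants are reused in the final test, and a significant result at either look counts as a claim. Under the null, the two Z statistics are bivariate normal with correlation √t, where t is the information fraction. Overall error = 1 − P(|Z₁| < 1.96 and |Z₂| < 1.96). The documents do not give t, so a range is shown.

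| Information fraction t | √t | Overall two-sided error |
|---|---|---|
| 38/72 = 0.528 | 0.726 | 8.2% |
| 38/96 = 0.396 | 0.629 | 8.6% |
| 26/72 = 0.361 | 0.601 | 8.8% |
| 26/96 = 0.271 | 0.520 | 9.0% |

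These figures are for one endpoint. If the early look can lead to no claim, stopping or design change, only the final test counts and its error is 5%.

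**4. What would hold the level at t = 38/96.**

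- Interim P<.001 with a final test at .05: overall about 5.04%.
- O'Brien-Fleming-type spending: P<.0018 at the interim and P<.0492 at the end, overall 5%.
- The same threshold at both looks: P<.028 each.

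**5. How informative an early comparison would be.** With N = 38 and f = 0.25, λ = 0.0625 × 38 × 9 / 5 = 4.275 for m = 9, giving power 0.52. With the four planned time points, λ = 0.0625 × 38 × 4 / 2.5 = 3.8, giving power 0.48. An early comparison has about an even chance of missing the effect that the trial is sized to detect.

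**The case against.** The strongest reply is that the article never says the preliminary paper tests outcomes between arms, that the 38 are pooled into the final test, or that the trial could stop or claim efficacy on them. That is correct. The recorded halt was caused by the pandemic, not by data. Pooling is the natural reading, since there is one trial, one target of 96 and recruitment that resumed, but it is not stated. A reader might infer that type I error is inflated as the plan stands; the documents do not support that, and the 8.2% to 9.0% is conditional.

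A reader might also infer that the trial has no alpha control. A full protocol or analysis plan may deal with interim looks. What can be said is that the article announces mid-trial results alongside a single-look design.

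A third inference would be that blinding collapses. That does not follow. Aggregate results do not reveal anyone's allocation, and the article itself already describes how the two app versions differ. Researchers are acknowledged to be unblinded, and referring physicians are never described as blinded. HbA1c comes from venous blood, and the glucose events come mainly from meter downloads, so expectation bias would act chiefly on the self-report secondary outcomes.

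Finally, the Results section gives a date for submission, which is not public release, although the abstract speaks of publication. What stands after all this is that the article plans to report results while later participants are probably still completing self-report scales, and that the stated design has no place for a by-arm look.

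**Conclusion.** The point holds in a conditional form. The planned mid-trial submission is a stated action, and it sits badly with a single-look design at .05. If the preliminary paper compares arms, it is an unaccounted interim look that could bias self-reported outcomes for those still in follow-up and could influence data collectors and referral. The size of that bias and the number exposed cannot be derived from the article; the ceiling is 58 of 96 (60%).

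The error rate rises to about 8.6% (8.2% to 9.0% across plausible information fractions) only if the early participants are reused and either look at P<.05 counts as an efficacy claim. Otherwise the final test keeps 5%. The calculation assumes a two-sided test and one endpoint.

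**What to change.** Before submission, state that the preliminary paper will contain only pooled (not by-arm) baseline, recruitment, retention and usability data, and that by-arm outcomes will be withheld until the last T3 visit. State also whether the 38 participants enter the final analysis.

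If a by-arm look has already been made, disclose it as an interim look that supports no efficacy claim or design change. The alternative is to allow a claim only at a stringent level such as P<.001, with the final test at about .05. A threshold declared after the data have been seen is not a prespecified boundary, so the first option is cleaner. In either case, add a sensitivity analysis by recruitment period (before or after the halt).

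The cost is a narrower or later preliminary paper. No extra participants or visits are needed. The decision has to come before by-arm results are released, because the exposure cannot be reversed.

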**Figure 3 figure3:**
[figure not shown]
CONSORT (Consolidated Standards of Reporting Trials) flowchart of preliminary results of the trial. HbA_1c_: hemoglobin A_1c_.

## Discussion

### Principal Findings

The Healthcare CEO app distinguishes itself as one of the few evidence-based, multifunctional integrated apps specifically designed for individuals aged 16-25 years managing T1D. This study uses a double-blind, randomized controlled trial intervention, with anticipated outcomes aimed at enhancing disease knowledge, improving self-care skills, and strengthening self-efficacy in disease management. Additionally, training in effective communication skills is intended to reduce interpersonal and emotional distress, enhance QoL, and ultimately improve glycemic control outcomes. The strengths and limitations of this study are elaborated in the following sections.

### Strengths

The 6 major aspects of diabetes self-management are physical activity, nutrition, blood glucose testing, medications or insulin injections, health feedback, and education. However, existing diabetes management apps focus only on 2 to 3 of these aspects on average. App developers should work closely with health care providers and patients to ensure that the developed apps address patients’ health care needs [53]. Our app differs from the majority of commercially available apps in that it contains the following distinctive features: (1) the app content has been designed based on a series of empirical studies [5,23,42] to ensure that it fulfills the needs of the users; (2) the app contains diverse content across 11 interfaces instead of being limited to 2 or 3 aspects; (3) the See Here: Diet and Exercise interface allows for easy and convenient recording of carbohydrate and calorie intake and exercise intensity; (4) the CEO Knowledge Base contains specific content targeted at patients in the transition phase, which is divided into basic and advanced knowledge, for perusal on a need basis; (5) themed discussions can be organized in the CEO Chat Rooms interface, during which users can discuss their needs and expert suggestions can be provided; (6) an SOS Calls function is provided for users transitioning from the dependence to independence phases, so that they can seek help from trusted individuals when needed; and (7) a points system, in which points can be exchanged for gift vouchers, is used to reward users for app use. With the above features and added emphasis on enhancing treatment fidelity, we anticipate that our results will indicate high effectiveness in diabetes self-management among patients with T1D in the transition phase due to our app-based intervention.

### Limitations

This study design has several limitations. First, the app usage may be limited by an unstable internet connection, which could impact the effectiveness of our app-based intervention. Second, in addition to providing gift vouchers to enhance the motivation and efforts of the participants, we also factored in an allowance during sample size estimation to minimize the effects of participant withdrawals. Third, because of the nature of the study, the researchers cannot be blinded during the study implementation, which may lead to potential biases. To address this issue, researchers must adhere to strict intervention principles to minimize the impact on the study results. Finally, the Healthcare CEO app was developed and will be evaluated based on Taiwanese participants with T1D in the transition phase. Therefore, caution will have to be exercised, and cultural differences will be considered when interpreting the study results.

### Conclusions

Patients with T1D transitioning from adolescence to early adulthood are in extreme need of support from health care providers and primary caregivers. The Healthcare CEO app developed in this study differs from current commercially available apps in that the functions desired by transitioning adolescent patients, as indicated by the empirical results obtained from previous qualitative and quantitative studies, have been integrated into the app to the best of our ability. In other words, this app is the first multifunctional app targeted at the needs of patients with T1D in the transition phase from adolescence to early adulthood. Our study protocol consisted of strategies formulated to enhance the treatment accuracy of the intervention measures. Such strategies make it possible to increase the objectivity of intervention effectiveness evaluation. The findings can serve as a reference for further applications to the clinical care of patients in the transition phase.

## Abbreviations

CONSORT: Consolidated Standards of Reporting Trials
DKQ: Diabetes Knowledge Questionnaire
HbA1c: hemoglobin A_1c_
QoL: quality of life
T1D: type 1 diabetes
T2D: type 2 diabetes
